#### **10.5 Incentives (if applicable)**

The maximum compensation for participants is 125 euros. For each missing blood sampling sessions, 30 euros will be subtracted from the maximum compensation (unless there were any valid reasons not to do the blood sampling, e.g. being sick/ urgent interferences). For every missing main questionnaire (completed three times; in week 0, 4 and 8), 5 euros will be subtracted from the compensation. In addition, 2,50 euros will be subtracted from the compensation for each incomplete weekly questionnaire upload (including 5 short daily questionnaires).

## 11. ADMINISTRATIVE ASPECTS, MONITORING AND PUBLICATION

### 11.1 Handling and storage of the data and documents

A data sharing agreement between CG selections and TU/e will be constructed regarding data sharing of participant names, phone numbers, e-mail addresses and home addresses. After a selection of participants is made based on the in- and exclusion criteria and interest to participate, participants will be contacted by the TU/e researcher for explanation of the study, participant information, and signing the consent form. All participants who signed the consent form and are allocated to one of the two groups (intervention vs. control), will receive a Participant ID with which the questionnaires are completed, and with which the serum 25(OH)D are transferred from DVU to the TU/e research team. Access to the key/link between the assigned number/code and names are saved in a secured local environment at the TU/e. An independent researcher at the Human-Technology department will pseudonymize (double code) the data received from DVU and obtained from the online questionnaires before sending these to the data-analyst. The double coding key will also be saved in a secured local environment at the TU/e. Data is not shared with, or stored at Signify. Analyses and reports are only on the group level (aggregated data) and not on the individual level. To protect privacy, coded data related to the pilot will be stored locally at the TU/e local server encrypted with a password. Data will be stored for a minimum of 15 year.

In order to prevent unnecessary data collection and unnecessary sharing the following actions are in place. For the blood sampling the participants will be in contact only and directly with medical partner DVU, who will do the blood sampling and the blood sample analysis. After 5 days of the analysis the remaining blood samples will be destroyed as medical waste. The laboratories will share the coded analysis results with TU/e. The independent researcher at TU/e pseudonymizes (double codes) the incoming data before sending the data set to the responsible investigator who will do the analyses. In this way, the researcher doing the analyses cannot identify individual participants in the final dataset. Participants can change their mind about including their data in the analysis until 24 hours after the final measurement day of the study.

All other data (questionnaire data) are stored locally at the TU/e server (encrypted, coded data). Access to the data will be limited to the responsible researchers. Data will additionally be protected by a strong password generated by a Microsoft approved password generator.

### 11.2 Monitoring and Quality Assurance

The WMO requires on-site monitoring for drug related research conform the ICH-GCP regulation (2005/28 EG). However, in case the clinical trial is not related to drugs and still WMO obligatory monitoring is not legally required. The intervention of the proposed clinical trial is a lighting intervention and not a drug. Therefore, a request for exemption is made.

### **11.3 Amendments**

Amendments are changes made to the research after a favourable opinion by the accredited METC has been given. All amendments will be notified to the METC that gave a favourable opinion.

### **11.4 Annual progress report**

An annual progress report will be sent to the METC. Since the pilot study is estimated to run from September till January including data gathering, analysis and reporting, the team will supply the end report two months after the end of the study the latest.

### **11.5 Temporary halt and (prematurely) end of study report**

The METC will be notified immediately of a temporary halt of the study, including the reason of such an action.

### **11.6 Public disclosure and publication policy**

The first aim of this pilot study is to explore the effectiveness of adding artificial UVB in general lighting solutions to sustain sufficient serum 25(OH)D in office workers. Secondary aims encompass effects on sleep quality and fatigue. The research team at TU/e will therefore report the results of this field study by means of an internal report and presentation for Signify. In addition, a publication in a peer-reviewed journal about the objective parameter (serum 25(OH)D) and correlational data about the questionnaires (sleep and fatigue) will be considered.

## 12. STRUCTURED RISK ANALYSIS

To ensure the newly developed prototype is safe to use in the clinical trial, a risk assessment has been conducted to identify potential risks and to take appropriate actions to alleviate these identified risks by (1) inherent safety by design, (2) protective measures in the medical device itself or in manufacturing process and (3) information for safe use. The risk assessment team included technicians, system architects, quality control people, photobiological safety experts both internally and externally, external UV-B expert, approbation specialists both internally and externally, human subject study experts and clinicians.

**The personal desk-based lighting device carries a CE mark with document no FS484F UV-B DoC**  
(D6\_8 CE Declaration of Conformity (FS484F UVB DoC))

### 12.1 Identified risks

#### 12.1.1 *Mechanical, thermal, and electrical*

Since the newly-developed luminaire prototype is based upon an existing commercially available architecture, the potential effects of failure in relation to the mechanical and electrical requirements were focused on those parts that were modified i.e. the head of the luminaire that could potentially change

- the mechanical stability
- thermal properties due to the change in LEB boards,
- material stability due to the UV-B LED
- electrical properties
- the stability of the diffuser window
- driver properties

Additional mechanical, thermal and electrical measurements were conducted to identify the potential risks severity and occurrence. The learnings were translated into construction improvements (safety by design) via protective measures in the device itself or prevention guidelines in e.g. the manual, participant information and research protocol (information for safety). Table 4 gives an overview of the risk analysis and mitigation. For more details we refer to *D1 Investigators brochure and risk analysis\_v2*.

**Table 4** Summary of the main identified risks, associated risk mitigation measures and remaining residual risk.

| Overview risk analysis and mitigation |                                     |                                                                                                                                                                                                                                                                                                                                                                                                                                                                                                                                                   |                       |          |                |
|---------------------------------------|-------------------------------------|---------------------------------------------------------------------------------------------------------------------------------------------------------------------------------------------------------------------------------------------------------------------------------------------------------------------------------------------------------------------------------------------------------------------------------------------------------------------------------------------------------------------------------------------------|-----------------------|----------|----------------|
| Risk category                         | Item                                | Taken measure                                                                                                                                                                                                                                                                                                                                                                                                                                                                                                                                     | Overall residual risk |          |                |
|                                       |                                     | inherent safety by design                                                                                                                                                                                                                                                                                                                                                                                                                                                                                                                         | occurrence of failure | severity | classification |
| Mechanical, thermal and electrical    | mechanical stability                | *weight delta is less than 1 %                                                                                                                                                                                                                                                                                                                                                                                                                                                                                                                    | 1                     | 1        | Negligible     |
|                                       | thermal properties                  | *max operating T is 31°C @ 20°C; far below max touch temperature of the housing and far below max operating temperature of the components                                                                                                                                                                                                                                                                                                                                                                                                         | 1                     | 1        | Negligible     |
|                                       | material stability                  | *an UV resistant double isolated wiring (confirm IEC60598) is used                                                                                                                                                                                                                                                                                                                                                                                                                                                                                | 1                     | 1        | Negligible     |
|                                       | EMC properties                      | *electrical class 1                                                                                                                                                                                                                                                                                                                                                                                                                                                                                                                               | 1                     | 1        | Negligible     |
|                                       | stability diffuser window           | *the diffuser window is fixed by mechanical design tightening the diffuser between two plates
* Additional support by chicken wire                                                                                                                                                                                                                                                                                                                                                                                                             | 3                     | 3        | Tolerable      |
|                                       | drivers                             | *maximum current is fixed to prevent an over drive of the UV-B LED
*maximum current can not be changed by e.g. an app                                                                                                                                                                                                                                                                                                                                                                                                                          |                       |          | Negligible     |
|                                       | malfunctioning of the luminaire     | *prolonged lifetime test did not show any malfunctioning or stability changes                                                                                                                                                                                                                                                                                                                                                                                                                                                                     | 1                     | 1        | Negligible     |
| photobiological safety                | exceeding 0.7 SED                   | *Bluetooth controller is secured via a pin-code to prevent misuse
*The max UV-B light output is limited by a firmware setting in the driver to a safe level:
-80mA
-MAX DALI level of 241
Single failure prevention of the setting is added by means of a 100mA fast fuse in the UV-B LED circuit.
*RCT clock turns the device automatically on and off
*Prototype is equipped with switch inside the luminaire head, which will switch off the UV-B LEDs in case the luminaire head is opened.
personalize dlighting device | 1                     | 1        | Negligible     |
|                                       | direct (prolonged) view to UV-B LED | *Protect installers: The prototype is equipped with a real time clock (RTC), which is setup at installation. After this setup, light will switch on at specified time stamps as agreed in the test protocol.
At power on, the luminaire will switch on at a dimmed white light level. UV-B will remain off. From next daily cycle schedule point, the light level will be set to the desired level. From that moment, the RTC will set the light in a daily cycle.                                                                             | 1                     | 1        | Negligible     |
|                                       | unawareness UV-B irradiance         | * luminaire is supplied with warning signals
* User information and education is available                                                                                                                                                                                                                                                                                                                                                                                                                                                     | 5                     | 3        | Tolerable      |
|                                       | prolonged skin exposure             | * The ultra-low daily dose is five-fold lower than the guideline to prevent sunburn for skin type 1.                                                                                                                                                                                                                                                                                                                                                                                                                                              | 1                     | 8        | Tolerable      |

### 12.1.2 **Photobiological safety**

While potential risks related to the lighting intervention are expected to be minimal, exposure to the personal desk-based lighting intervention may result in undesirable experiences such as experienced discomfort (e.g., visual discomfort or eyestrain) or headache. Additionally, the use of the study protocol might result in distressing effects in relation to an oversensitivity to UVB, unknown at the start of the study. In that case if the participant notices a potential distressing effect, he/she can stop immediately.

Negative effects of UVB are associated to the formation of cyclobutylpyrimidine dimers in DNA contributing to the mechanism of erythema and sunburn formation. To place the UV dose applied in this study in context, the dose received throughout a full working day would be equivalent to 10 minutes in bright sunlight at lunchtime on a summer day in Northern Europe. It is clearly below the daily dose for the EU Safety Directive 2006/25/EC, and well below the erythema (sunburn) threshold for all skin types. Individuals who suffer from photosensitivity disorders, take photosensitizing medication or have had treatment for skin cancer will be excluded from the trial.

The main identified risk factors associated with these photobiological safety aspects:

- exceeding the 0.7 SED per day limit due to long office hours
- direct (prolonged) viewing of the UVB LED at short distances
- lack of awareness of UVB irradiance from the source

have been mitigated by design, protective measures and information for safe use (see table 1 and *D1 Investigators brochure and risk analysis\_v2* ).

As an additional measure, the newly developed luminaire is equipped with a real time clock ensuring that the exposure to ultra low doses UV-B will not exceed 8 hours and 20 minutes. After the first blood sampling has taken place, the luminaire will be powered by putting the plug in the mains socket by the research team. When the luminaire is connected to power it will start with dimmed white light and no UVB. A small amount of white light is emitted to indicate that the luminaire is ON. At noon or when powered after 13.00 hr, the next morning, the luminaire will switch ON (full brightness and UVB) according the preset schedule. at 8.50 hr. At 17.10 hr both the white and UV-B light will turn off. This behavior will also occur in case of a power cycle / disturbance in power. When the luminaire remains plugged, the luminaire will automatically switch ON (full brightness and UVB) at 8.50 hr. At 17.10 hr both the white and UV-B light will turn off. This will be repeated for all days during the study period as long as the luminaire is powered.

The contributory risk of developing skin cancer by exposure to ultra low doses of artificial UVB during a 2-month period is considered to be very low:

- The ultra-low daily dose is five-fold lower than the guideline to prevent sunburn for skin type 1.
- The recommendation of the KWF for required healthy sun exposure is in line with what is intended in this study.
- The potential protective effects of vitamin D to attenuate inflammation from sunburn

For more details see appendix III in *D1 Investigators brochure and risk analysis\_v2*.

In summary, if the application precautions are considered to make the luminaire safe for the intended application, as described in the photobiological safety photobiological hazard (European directive 2006/25/EC), and the device can be regarded safe to use under application conditions according to IEC 62471 .

(supporting documents *D6\_1 Analysis of Signify Luminaires\_Final*, *D6\_7 Manual-Installer v2.0*, *E4 manual user*).

## 12.2 Application precautions

The luminaire is calibrated at safe light output values when used as intended (at a distance of >80 cm). Respecting the indicated minimum application distances (up to 80 cm) keeps the Actinic UV exposure within Risk Group Exempt limits, which allows for a continuous exposure of 30000 sec per day (8 hrs and 20 minutes). Being at a closer distance (up to 35 cm) to the luminaire would allow for a continuous exposure of 10000 sec per day (2 hrs. and 45 minutes). At distances closer (looking and staring into the luminaire at close distance) than the indicated 35 cm, a continuous exposure of the luminaire of 1000 sec per day is allowed (15 minutes), but this should be avoided.

Prior to placement the general desk illumination should be measured to check compliancy with local home office illumination. The lighting units are internally set by the manufacturer to come on at 08:50 hr and go off at 17:10 hr when powered, restricting both the lighting and the UV supplementation to these hours of the day, so that a daily dose may not be exceeded. Controls are only accessible to trained personnel. The UV radiation dose will be monitored throughout the trial by trained personnel to ensure that the UV output of the units remains constant (see *D6\_7 Installer manual v2.0*).

As extra precaution, the UV-B irradiance of the lamp will be regularly checked during the study period by the technically trained person (see *D6\_7 Installer manual v2.0*):

- Via solar meter model 6.5 (UV) at 20 cm of the head of the luminaire. UVB irradiance levels on a weekly basis to ensure a consistent dose during the pilot study monitored by a point measurement
- The relative stability will also be monitored through a continuous daily dose measurement is conducted by placing wear shade dosimeters at the desk. The watch is placed a charger.

The desk-based intervention device is labelled with caution labels and a warning not to stare directly into the luminaire. The additional white lighting provides for an additional cue to the users that UVB is irradiated. To ensure proper usage in the application and operating of this engineering sample, participants are asked to adhere to the following guidelines (see *E4 Manual user* and **Figure 5**):

- You do not have to turn on or off the luminaire. This will be conducted automatically.
- Please prevent direct view to the luminaire head
- Please, prevent prolonged exposure to distances shorter than 80 cm.
- Your desk has been taped to indicate the area of sufficient user's UV-B exposure. Please, try to work as much as possible in this area to receive the intended safe dose of UVB irradiation.
- Please, indicate to others in the home office, not participating the test, to be placed at a minimal distance of 1.6m to the luminaire.
- Please, unpower the device if you experience skin redness or eye strain and please report the event.
- Any damage or unexpected behavior should be reported directly

Co-workers, not participating the test, should be placed at a minimal distance of 1.6m to the luminaire.

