### 4.3 Exclusion criteria

The exclusion criteria include:

- Current pregnancy, breast feeding or a desire to become pregnant
- Having children at home aged 10 years or younger
- Having malignant skin conditions in the past or currently
- Photosensitive medical conditions or photo-sensitising drugs
- Users of medicines and/or cremes mentioning in the prescription as side effect extra sensitivity to the sun / interaction with sun exposure
- Planned use of sun beds, or sunbed use during the past 4 weeks
- Currently taking or planning to take oral vitamin D3 supplements or have been taking D3 supplements during the past 4 weeks.
- High vitamin D levels at the start of the study (>375 nmol/L) which need medical attention [41]

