## 5. TREATMENT OF SUBJECTS

All home office workers who will participate in the study will be asked to continue their work as they are used to do. During the workday all participants are exposed to the illumination of the existing general indoor lighting in their home. Depending on their desk location, participants may be exposed to daylight entering the office space through windows. This additional light will not contain UVB irradiance as UVB irradiance is absorbed by the window glass.

In addition to the standard lighting the **intervention group** will receive an additional personal desk-based luminaire that is positioned at the side of participant's home desk. The participants in the intervention group will be asked to be seated closer to one side of the desk, where the free floor standing luminaire is positioned, in order to sit more effectively under the luminaire. The area to be seated will be marked on the desk with stickers and tape. Figure 4 demonstrates the desk-based intervention lighting device placed at the side of the desk. Care is taken that the distance between the participant receiving a luminaire and the neighbor (non-participating) colleague/family member is more than 1.6 m to prevent that the (non-participating) colleague/family member is exposed to the ultra-low doses of UVB. The designated workspace of the control group is not altered for the purpose of the study. Control participants will experience only the existing general lighting in their home office).

The desk-based luminaire will emit a continuous ultra-low and safe daily artificial UVB irradiance (actinic UV) of less than 6 mW/m^2 at 20 cm resulting in a received dose by the office worker sitting at his/her desk of about 0.45 SED ((UVI = 0.06) during office hours. The lamps are turned on automatically at 8.50 and off at 17.10 hr. A longer (over)-exposure is therefore not possible. Both groups can do their daily work as they are used to do. Both the participants and the people living in their home will be advised to respect the indicated minimum application distance (80 cm). This minimum application distance keeps the Actinic UV exposure within Risk Group Exempt limits, which allows for a continuous exposure of 30000 sec per day (8 hrs. and 20 minutes) according to the IEC62471 (see form *D6\_2 Photobiological safety IEC 62471 ed 1.0*).

[figure not shown]

**Figure 4.** A picture of a currently designated workspace equipped with the desk-based lighting device.

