#### 10.4.3 *Potential risk*

While potential risks related to the lighting intervention are expected to be minimal, exposure to the personal desk-based lighting intervention may result in undesirable experiences such as experienced discomfort (e.g., visual discomfort or eyestrain) or headache. Additionally, the use of the study protocol might result in distressing effects in relation to an oversensitivity to UVB, unknown at the start of the study. In that case if the participant notices a potential distressing effect, he/she can stop immediately.

Negative effects of UVB are associated to the formation of cyclobutylpyrimidine dimers in DNA contributing to the mechanism of erythema and sunburn formation, generally occurring during prolonged exposure at very sunny days ( $UV-I > 5$ ). To place the UV dose applied in this study in context, the dose received throughout a full working day would be equivalent to 10 minutes in bright sunlight at lunchtime on a summer day in Northern Europe. It is clearly **below the daily dose for the EU Safety Directive 2006/25/EC, and well below the erythema (sunburn) threshold for all skin types**. Individuals who suffer from photosensitivity disorders, take photosensitising medication or have had treatment for skin cancer will be excluded from the trial. The main identified risk factors associated with these photobiological safety aspects:

- exceeding the 0.7 SED per day limit due to long office hours
- direct (prolonged) viewing of the UVB LED at short distances
- lack of awareness of UVB irradiance from the source

have been mitigated by design, protective measures and information for safe use.

The contribution to risk of developing skin cancer by exposure to ultra low doses of artificial UVB during a 2-month period is considered to be negligible:

- The ultra-low daily dose is five-fold lower than the guideline to prevent sunburn for skin type 1.
- The recommendation of the KWF for required healthy sun exposure is in line with what is intended in this study.
- The potential protective effects of vitamin D to attenuate inflammation due to sunburn

In summary, the application precautions are considered to make the luminaire safe for the intended application, as described in the photobiological safety photobiological hazard (European directive 2006/25/EC), and the device can be regarded safe to use under application conditions according to IEC 62471 .

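### In the protocol text shown, no lamp-stop trigger covers a user who becomes photosensitised after enrolment until a reaction appears (minor; cheap to close)

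*Protocol*

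**What the plan says.** Section 4.3 of the protocol excludes "Photosensitive medical conditions or photo-sensitising drugs" and, separately, "Users of medicines and/or cremes mentioning in the prescription as side effect extra sensitivity to the sun / interaction with sun exposure". Section 10.4.3 uses this as a risk control: "Individuals who suffer from photosensitivity disorders, take photosensitising medication or have had treatment for skin cancer will be excluded from the trial". Sections 4.1, 7.3.2 and 7.4 have the criteria confirmed by e-mail and then by telephone, before enrolment.

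On dose, Section 5 describes automatic daily operation, "resulting in a received dose by the office worker sitting at his/her desk of about 0.45 SED". Section 10.4.3 lists "exceeding the 0.7 SED per day limit due to long office hours" among the risks designed out, and adds "The ultra-low daily dose is five-fold lower than the guideline to prevent sunburn for skin type 1". It also says that the dose is well under the sunburn threshold whatever the skin type, and compares a full working day to about ten minutes of midday summer sun.

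On stopping, the user guideline in Section 12.2 is "Please, unpower the device if you experience skin redness or eye strain and please report the event". For an oversensitivity not known at entry, Section 10.4.3 says "In that case if the participant notices a potential distressing effect, he/she can stop immediately", and Sections 12.1.2 and 12.3 repeat this. Section 8.2.1 provides for contact after an adverse event. Section 7.5 gives voluntary withdrawal.

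**The concern.** For photosensitised people the protocol's safeguard is not to expose them. It does not claim that the dose is safe for them. A person's status can change during eight weeks, for example through a new prescription, a new cream or a new diagnosis. From then on the safeguard no longer works for that person, and the first stated signal to switch off is the kind of skin or eye reaction that the exclusion is meant to avoid.

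What is at stake is participant safety on a small scale. The validity of the primary comparison is not in question.

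**Working it through.** **Step 1: what acts before a symptom, and what acts after.**

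| Control | Section | Acts before a symptom? | Triggered by new photosensitivity? |
|---|---|---|---|
| Exclusion of conditions, drugs, creams | 4.3, 10.4.3 | Yes | No, checked before enrolment |
| Timer, firmware limit, low dose | 5, 6.1, 12.2 | Yes | No, the same for all users |
| Unpower the lamp on redness or eye strain | 12.2 | No | Only through a reaction |
| Stop on a noticed effect | 10.4.3, 12.1.2, 12.3 | No | Only through a reaction |
| Contact after an adverse event | 8.2.1 | No | Only through an event |
| Voluntary withdrawal | 7.5 | Possible | Only if the person thinks of it |

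The criteria in Section 4.3 on sunbeds, oral vitamin D and pregnancy cover plans as well as current status. The two photosensitivity criteria do not.

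Nothing described after enrolment asks about medicines. The daily diary records desk presence, time outside and exposed skin. The questionnaires cover fatigue, sleep, vitamin D in food and optional comments. Meanwhile the lamp switches itself on each scheduled day while powered, and Section 12.2 asks users to work in the taped area as much as they can. A user who follows that text exactly stays exposed.

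**Step 2: the protocol's dose figure.** Inputs: 0.45 SED per day, 100 J/m² per SED (abbreviation list), 30,000 s per day (Section 5).

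- 0.45 × 100 / 30,000 = 0.0015 W/m².
- With the usual UV Index scaling of 40 per W/m² (an assumption, not stated in the protocol): 0.0015 × 40 = 0.06, as stated.

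**Step 3: dose against the stated limit (0.7 SED per day).**

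- Full desk presence: 0.45 / 0.7 = 64%.
- Half dose (0.225 SED, Table 2): 0.225 / 0.7 = 32%.
- At the stated ceiling of 0.5 SED: 0.5 / 0.7 = 71%.

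No stated limit is exceeded.

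**Step 4: the only numerical sunburn margin.** It is five-fold, for skin type 1. If it refers to 0.45 SED, the implied guideline is 5 × 0.45 = 2.25 SED. Participants are type II or III, for whom no figure is given, so their margin may be larger. The protocol does not say how far a medicine or condition lowers a person's threshold. Purely as an assumed range, let the threshold fall by a factor k:

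| k (assumed) | Margin at 0.45 SED = 5/k | Margin at 0.225 SED = 10/k |
|---|---|---|
| 2 | 2.5 | 5 |
| 3 | 1.7 | 3.3 |
| 5 | 1.0 | 2 |

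These rows only show that a skin-type margin cannot be read across to a photosensitised person. They are not an estimate of harm.

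**Step 5: cost of switching a lamp off.** Section 4.4 plans on a difference of 8.8 nmol/L with 14 lamp users. If one user had the lamp off for all eight weeks and got no effect, the mean difference would fall by 8.8 / 14 = 0.63, to about 8.2 nmol/L. A switch-off partway through costs less.

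**The case against.** The strongest reply has three parts.

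First, the Section 12.2 line is a sound precaution and contradicts nothing, so the point is a missing line and not an error. This stands in part: nothing is misstated. But the protocol does fix the stop triggers, and for this group they fire at the reaction that the exclusion exists to prevent. That is a safety rule which belongs in the protocol.

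Second, the instruction may exist elsewhere. Section 12.2 refers to the user manual and to Figure 5 with its caution labels, and Section 12.1.1 says that prevention guidelines also went into the manual and participant information. None of these is shown. This stands, and it limits the point to the text at hand. If the instruction is there, only the Section 7.5 sentence remains to be added.

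Third, the dose is very low and practical routes exist. Participants have been asked about these medicines twice, and the medicines carry their own warning. Lamp users are shown how to switch the lamp off. Participants can comment or contact the investigator, and they receive a letter for their general practitioner. This also stands as a reason to rank the point low. However, no text shown links these routes to a new medicine or diagnosis. Section 7.3.4 has the questionnaire data downloaded at the end of the study, so a written comment might not be read in time. The regular irradiance checks verify the lamp, not the user.

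A reader might infer that photosensitivity is controlled only by exclusion. The documents do not support that: the dose caps, symptom stops, adverse-event contact and voluntary withdrawal all exist.

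**Conclusion.** The point holds as a minor gap. Before symptoms, the protocol as shown relies on exclusion at screening plus a general low-dose cap. After enrolment, no trigger is tied to new photosensitivity, so an affected lamp user is not told to stop ahead of a reaction.

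It concerns at most 14 people, at about 0.45 SED per day, below the 0.7 SED limit and stated to be well under the sunburn threshold for all skin types. Incidence is not given and the number affected could be zero. The conclusion assumes that the unseen manual, labels and participant information do not already carry the instruction.

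Two stronger readings should be resisted. One is that the lamp dose is unsafe for photosensitised users: the protocol gives no margin for them in either direction, and the threshold falls in Step 4 are assumptions. The other is that the primary analysis is biased or loses data: nothing in the documents shows that.

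**What to change.** 1. Add to the Section 12.2 user guidelines, unless the manual, labels or participant information already say it: 'Unpower the device and contact the responsible researcher before starting any medicine or cream with a sun-sensitivity warning, or if newly diagnosed with a photosensitive condition; do not delay the treatment itself.'
2. Add to Section 7.5: 'In that case the investigator stops lamp exposure; the week 4 and week 8 blood draws continue.' Section 9 analyses only people with both a baseline and a final sample, so keeping the draws keeps the person in the primary analysis.

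The final clinical wording is for the sponsor's clinicians. The cost is one line, one sentence and notification to the ethics committee. The statistical downside is slight dilution of the group difference, at most about 0.63 nmol/L per affected person under the planning assumption. The switch-off date should be noted, because the exploratory dose model in Section 9 computes dose from desk presence and clothing and would otherwise credit exposure that did not occur. A weekly medication question is not recommended: it would need someone to read the answers every week.
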